## Methods

### Design

This study uses a hybrid design, which was developed to advance implementation science by examining both implementation processes and effectiveness in a single study [25, 26]. We give equal attention to both processes and effectiveness evaluation, a balanced design recommended where there is already evidence supporting efficacy [25].

We use a stepped wedge design to evaluate effectiveness, with staggered introduction of the intervention in three communities in randomly assigned order (Fig. 1). The stepped wedge design [27–29] has the advantage that all groups receive the intervention, which is ethically important, especially in a community intervention. This design is efficient because the repeated measures allow participants to serve as controls until the intervention is introduced in their community. In each community, the first 144 adults and 144 youth are asked to both receive the intervention and to participate in the effectiveness evaluation. Outcome measures are assessed at baseline and after each community rolls out the intervention.

**Fig. 1 Fig1:**
[figure not shown]
Stepped wedge cluster randomized design with evaluations at Waves 1-4

### Setting and sample

The study takes place in Phalombe District in southern Malawi. The district has a population of nearly 350,000 [30]. In consultation with District leaders, we identified one sub-district area as the most appropriate place to test the 3-step model. This area is the largest in the district; a third of the district’s population resides there. The leaders in that area selected three communities as sites for implementation.

The sample includes both the implementation partners described above, who share their perspectives on the implementation process (Aim 2), and community members, who participate in the intervention (Aim 1) and its effectiveness evaluation (Aim 3). District level leaders from government, the health sector and traditional leaders collaborate for implementation and are included in qualitative evaluation. Implementation partners in each of the three communities include a coordinating committee that will oversee implementation and the trained peer leaders. Eligibility criteria for implementation partners include being in the designated role and willingness to participate.

The community member participants include adults and youth (ages 13–19) who take part in the 7-session peer group intervention. The first 144 adults and 144 youth in each community participate in both the peer group intervention and the repeated effectiveness surveys. Participants also provide information for the process evaluation during periodic group session observations, focus groups and repeated individual interviews. Eligibility criteria for community participants include residing in the designated community and, for youth, being within the designated age range and having parental permission to participate if under age 18. We subsequently increased the number of youth recruited, because they are more likely to move away over time.

#### Power analysis, Aim 2 effectiveness

We performed a power analysis for the stepped wedge effectiveness component to determine sample size. Conventional power calculation programs are not able to consider both the intra-class correlation (ICC) for the intervention clusters, and the ICC for repeated measures of individuals over time. Therefore, we performed 1000 simulations using the stepped wedge design, for both continuous outcomes (analyzed using mixed-effects regression) and binary outcome (analyzed using mixed-effects logistic regression) [31, 32]. We conservatively set cluster-level ICC to be 0.10, based on two previous community or classroom studies that found an ICC of 0.05 [33, 34]. Individual-level ICC was set to range from 0.2 to 0.4, as is typical for correlations between repeated measurements of an individual. We set retention rates at 85, 80, and 75% at waves 2 through 4, a conservative estimate given our prior study with 80% retention at 18 months. Expected effect sizes (0.10 to 0.20 for continuous outcomes; odds ratios ranging from 1.2 to 2.2 for dichotomous outcomes) were based on significant outcomes in our previous efficacy study [10, 11] or, for comprehensive HIV knowledge and sexually transmitted infection (STI) prevalence, a 2010 national survey [35]. With 80% statistical power, the sample of 432 persons (youth or adults) with retention rates of 75% at the last wave, supported a minimum detectable effect size of 0.13 for continuous outcome variables, and a minimum detectable odds ratio of size 1.36. Thus, we have sufficient power to detect all expected intervention effects for outcome variables for adults and youth separately.

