**Methods:**

Three communities in southern Malawi begin implementation in randomly-assigned order using a stepped wedge design. Our evaluation sample size of 144 adults and 144 youth per community provides sufficient power to examine primary outcomes of condom use and HIV testing. Prior to any implementation, the first participants in all three communities are recruited and complete the Wave 1 baseline survey. Waves 2–4 surveys occur after each community completes roll-out. Each community follows the model’s three steps. During Prepare, the community develops a plan and trains peer group leaders. During Roll-Out, peer leaders offer the program. During Sustain, the community makes and carries out plans to continue and expand the program and ultimately obtain local funding. We evaluate degree of implementation success (Aim 1) using the community’s benchmark scores (e.g, # of peer groups held). We assess implementation process and factors related to success (Aim 2) using repeated interviews and observations, benchmarks from Aim 1 and fidelity assessments. We assess effectiveness of the peer group intervention when delivered by communities (Aim 3) using multi-level regression models to analyze data from repeated surveys. Finally, we use mixed methods analyses of all data to assess feasibility, acceptability and sustainability (Aim 4).

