#### Aim 3 (effectiveness analysis)

The effectiveness of the *Mzake* intervention when offered by communities is determined by survey data and STI symptom interviews with a nurse at Waves 1–4. We will complete a CONSORT diagram showing recruitment, retention and loss to follow-up at each wave. We then examine significant factors associated with lost to follow-up. Identified attrition factors will be controlled in later analyses.

To evaluate the effectiveness of the intervention in improving HIV-related outcomes, we will use multi-level mixed-effects regression (for continuous outcomes) and logistic regression (for dichotomous variables) models [51]. These methods allow us to take into account time of implementation as well as lack of independence among repeated measurements and members of the same peer group. The hierarchical structure of the data is conceptualized as repeated outcome measures (level 1), nested within individuals (level 2) and nested within peer groups (level 3). Random individual and peer group effects will account for correlations between repeated measurements and between individuals from the same peer group. Intervention condition will be a time-varying covariate that reflects the stepped-wedge design in which individuals receive intervention at different stage of the study. Site and demographic factors (both individual level and community level) will be treated as fixed-effects covariates to account for differences. Time trend interactions for intervention and imporant factors will be tested to identify differential effects over time. Youth and adult data will be analyzed both together and separately. Model selections for the number of random effects and the variance-covariance structures for the outcome variables will be performed using likelihood ratio tests. Backward selection will be employed for the fixed effects. *Aim 3 analysis identifies effectiveness overall and by site.*

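### The stated detectable effect of 0.13 SD reproduces only without a wave term; with wave fitted it is about 0.20–0.25 SD, and the sufficiency claim already fails on the paragraph's own figures

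*Protocol article*

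**What the plan says.** The Design section describes a stepped wedge "with staggered introduction of the intervention in three communities in randomly assigned order". It adds: "Outcome measures are assessed at baseline and after each community rolls out the intervention". This gives four waves: none of the three communities is exposed at Wave 1 and all three are at Wave 4.

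The power section (*Power analysis, Aim 2 effectiveness*) reports 1000 simulations analysed by mixed-effects linear and logistic regression. On the cluster correlation it states: "We conservatively set cluster-level ICC to be 0.10, based on two previous community or classroom studies that found an ICC of 0.05". The individual-level ICC runs from 0.2 to 0.4 and retention is 85, 80 and 75% at Waves 2 to 4. The anticipated effects are 0.10 to 0.20 for continuous outcomes and odds ratios of 1.2 to 2.2 for binary ones. For a power of 80% and 432 people in each age group, the stated result is that the sample "supported a minimum detectable effect size of 0.13 for continuous outcome variables, and a minimum detectable odds ratio of size 1.36". The paragraph then concludes that power suffices for every anticipated effect, in adults and youth separately. The abstract says that the sample "provides sufficient power to examine primary outcomes of condom use and HIV testing".

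On time, *Aim 3 (effectiveness analysis)* says that the methods account for when implementation occurred, and that "Time trend interactions for intervention and imporant factors will be tested to identify differential effects over time". It names no wave main effect and applies backward selection to the fixed effects.

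**The concern.** In a stepped wedge, the share of communities exposed rises with calendar time by construction, here 0/3, 1/3, 2/3 and 3/3. Without a wave term, any general change in HIV testing or condom use over the study is credited to the intervention. With a wave term, much of the information on the intervention effect is lost. A power figure that matches only the model without wave therefore describes an analysis that the trial should not rely on.

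At stake is how a null result would be read. If readers believe that 0.13 SD was detectable with 80% power, a non-significant result looks like evidence that community delivery does not work, when power for that effect was below one half.

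**Working it through.** **Inputs from the article:** 3 communities × 144 = 432 per age group; 4 waves; exposure patterns 0111, 0011 and 0001; retention 100/85/80/75%; cluster ICC 0.10; individual ICC 0.2–0.4; 80% power.

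**Assumptions, because the article is silent:** two-sided 5%; monotone dropout; total variance 1. The individual ICC may include the cluster part (*inclusive*: person variance = ICC − 0.10) or be added to it (*additive*: person variance = ICC). Both were run.

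**Method.** Generalised least squares variance of the intervention effect, with community, person and residual variance components. MDE = (1.960 + 0.842) × SE. Power at effect d = Φ(d/SE − 1.96).

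**Step 1. The plan's own figure, no wave term**

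| Individual ICC | SE, inclusive | MDE | SE, additive | MDE |
|---|---|---|---|---|
| 0.2 | 0.0513 | 0.144 | 0.0482 | 0.135 |
| 0.3 | 0.0482 | 0.135 | 0.0449 | 0.126 |
| 0.4 | 0.0449 | 0.126 | 0.0412 | 0.115 |

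The range 0.115–0.144 brackets the stated 0.13.

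**Step 2. Wave fitted (linear and categorical wave agree)**

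| Individual ICC | SE, inclusive | MDE | SE, additive | MDE |
|---|---|---|---|---|
| 0.2 | 0.0890 | 0.249 | 0.0835 | 0.234 |
| 0.3 | 0.0835 | 0.234 | 0.0775 | 0.217 |
| 0.4 | 0.0775 | 0.217 | 0.0709 | 0.199 |

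Hand check of the inflation, for complete data with community effects removed. The within-community sum of squares of exposure over the 12 community-waves is 0.75 + 1.00 + 0.75 = 2.50. The part explained by wave is 3 × (0.25 + 0.0278 + 0.0278 + 0.25) = 1.667, which leaves 0.833. The SE therefore grows by √(2.50/0.833) = √3 = 1.73, in line with 0.0890/0.0513 = 1.73.

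**Step 3. Power with wave fitted (lowest and highest over Step 2)**

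- d = 0.10: 20% to 29%
- d = 0.13: 31% to 45%
- d = 0.20: 61% to 80%

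A 1000-run Monte Carlo check with site terms gave 73–88% at 0.13 without wave, 33–43% at 0.13 with wave, and 62–77% at 0.20 with wave.

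**Step 4. Can other readings rescue 0.13 with wave in the model?** One-sided 5% gives 0.176–0.221. Full retention gives 0.18–0.23. Pooling adults and youth (864 persons) gives 0.141–0.177. Using peer groups as clusters (12 per site assumed) widens the range only to 0.195–0.251. None of these reaches 0.13.

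**Step 5. Odds ratio.** The power section gives no control rate. As a rough conversion, log OR = MDE/√(p(1 − p)). Without wave, MDEs of 0.126–0.144 give 1.29–1.43 at control rates of 20–50%, which brackets 1.36. A random-intercept logistic model without wave gives 1.40–1.56 at 25–49% and 1.6–1.9 at 7–12%. So 1.36 is met only approximately, and only for common outcomes. With wave, at the control rates of 7–12% that the Background reports for HIV testing and adult condom use, the conversion gives about 1.8–2.7 and the logistic mixed model about 2.2–3.2.

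**Step 6. No modelling at all.** Stated minimums: 0.13 and 1.36. Smallest anticipated effects: 0.10 and 1.2. Since 0.13 > 0.10 and 1.36 > 1.2, the bottom of each range lies below what the paragraph says is detectable. Even without wave, power at 0.10 is only 50–68%.

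**The case against.** The article never says that wave was left out. It says that time is taken into account, cites simulation methods that are not shown here, and gives neither alpha nor the effect-size metric. If 0.13 were on a scale equal to half the standardised difference, the with-wave values would be about 0.10–0.125, although nothing in the text suggests such a scale. Pooling both age groups and testing one-sided at 5% would also bring the with-wave figure down to 0.125–0.157, but the article ties 0.13 to 432 persons. What stands of this is that the omission is a reconstruction and has to be worded as one.

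Three stronger readings are tempting, and the documents do not support them:

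- *No anticipated continuous effect reaches 80% power.* With additive ICCs and an individual ICC of 0.4, both compatible with the text, the with-wave MDE is 0.199 and an effect of 0.20 just reaches 80%.
- *The true detectable odds ratio is about 1.7, or the trial is underpowered for all its primary outcomes.* No single odds ratio can be named without a control rate. The Background's condom-use rates imply odds ratios of (25/75)/(12/88) = 2.44 for adults and (70/30)/(49/51) = 2.43 for youth. For youth this exceeds the with-wave minimum of 1.8–2.2 at control rates of 25–49%; for adults it lies within or above the ranges in Step 5. HIV testing is more exposed: (18/82)/(10/90) = 1.98 and (14/86)/(7/93) = 2.16, at control rates of 10% and 7%.
- *Calling the ICC of 0.10 conservative is an error that needs correcting.* Moving from 0.05 to 0.10 changes the with-wave MDE negligibly, and the direction depends on the convention: 0.243 to 0.235 in one, 0.248 to 0.249 in another. Nothing turns on the word.

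**Conclusion.** The point holds in two parts. On the stated inputs and a two-sided 5% test, 0.13 SD matches an analysis without wave. A time-adjusted analysis at 432 persons detects about 0.20–0.25 SD, roughly 1.7 times as much, so most of the anticipated 0.10–0.20 range falls below 80% power and only its upper end comes close or just reaches it. The width of the range comes from the individual ICC and its unstated convention. For binary outcomes only the direction is secure: fitting wave raises the minimum odds ratio, most of all for the uncommon outcomes.

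Separately, and free of any assumption, the conclusion that all anticipated effects are covered is contradicted by the numbers beside it.

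**What to change.** 1. Re-run the simulations with wave as a fixed effect in both the generating and the fitted model.
2. In the power section, state alpha and sidedness, whether the individual ICC includes the cluster part, and the control rate assumed for each binary outcome.
3. Replace 0.13 and 1.36 with the resulting figures for each outcome; expect about 0.20–0.25 SD for continuous outcomes.
4. In the Aim 3 analysis, keep wave in the model and exempt it from backward selection, so that the analysis matches the power calculation.
5. Amend the sufficiency sentences in the power section and the abstract to name the effects and outcomes for which 80% power is reached.

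The cost is a simulation re-run and some rewording. No extra enrolment or change in trial conduct is needed; the stated power becomes less favourable.

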## Background

Addressing HIV transmission in low-resource countries in sub-Saharan Africa is essential to meeting the UNAIDS 2030 goal of no new HIV infections [1]. Although new infections continue to decline, there were 1.8 million new infections globally in 2016, and 64% of these occurred in sub-Saharan Africa [2]. Nearly 40% of new infections occur among young people ages 15–24. Scaling-up evidence-based behavior change interventions can help prevent new infections by reducing knowledge gaps and risky sexual behaviors and increasing early testing and treatment.

Our research team developed an evidence-based behavior change intervention for HIV prevention and testing in rural Malawi, an African country hard hit by the HIV epidemic. This 7-session peer group intervention, called *Mzake ndi Mzake* (Friend-to-Friend, *Mzake*), is guided by Bandura’s social-cognitive learning theory [3] that emphasizes building self-efficacy, which has been linked with efficacy in previous meta-analyses and reviews [4–9]. Each session incorporates games and role-plays that rehearse specific steps needed for HIV prevention, such as discussing condom use with a partner. Importantly, the intervention is designed for all reproductive aged individuals regardless of age or gender. Using a quasi-experimental design, we compared a random sample of adults and youth in communities that received *Mzake* and control communities. People in the *Mzake* communities reported significantly more HIV prevention behaviors, including more condom use (Adults, 25% vs. 12%; Youth, 70% vs. 49%) and more HIV tests within the past year (Adults, 18% vs. 10%; Youth, 14% vs. 7%) [10–12].

With efficacy established, this intervention is ready for wider dissemination to other rural communities in Malawi. In the efficacy study, volunteer health workers served as peer leaders and provided training. However, persistent health worker shortages mean that Malawi’s health system does not have the capacity to lead community scale-up because they must meet expanding demands for HIV testing and treatment as well as other health needs.

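### The claim of sufficient power for all expected effects contradicts the plan's own detectable minima: effects from 0.10 and OR 1.2 are expected, but 80% power starts at 0.13 and OR 1.36

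*Protocol article*

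**What the plan says.** All the figures stand in one paragraph of the protocol article, Methods, Power analysis, Aim 2 effectiveness.

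- Expected effects: "Expected effect sizes (0.10 to 0.20 for continuous outcomes; odds ratios ranging from 1.2 to 2.2 for dichotomous outcomes". They are taken from the earlier efficacy study or, for HIV knowledge and STI prevalence, from a national survey.
- Sample and power: "With 80% statistical power, the sample of 432 persons (youth or adults) with retention rates of 75% at the last wave".
- Continuous outcomes: this sample "supported a minimum detectable effect size of 0.13 for continuous outcome variables".
- Binary outcomes: "and a minimum detectable odds ratio of size 1.36".
- Conclusion: "Thus, we have sufficient power to detect all expected intervention effects for outcome variables for adults and youth separately".

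The minima come from 1000 simulations of the stepped wedge design. The paragraph gives the ICCs and the retention rates. It does not give alpha, the outcome rate behind the binary minimum, or how time was handled.

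Two other places bear on the point. The Background gives the efficacy-study rates for condom use and HIV testing. Table 1 places a self-efficacy scale and a partner communication index under the safer-sex heading that it marks as primary.

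**The concern.** Both expected ranges begin below the matching detectable minimum: 0.10 is less than 0.13, and 1.2 is less than 1.36. The conclusion nevertheless covers every expected effect, and covers it within each age group. The three statements cannot all be true.

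Aim 3 asks whether the intervention works when communities deliver it, and the analysis section examines adults and youth separately as well as together. A reader who accepts the power sentence could take a non-significant result on a small-effect outcome as evidence that community delivery does not work. For effects at the low end of the plan's own ranges, such a result would be likely even if the expected effect were real.

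**Working it through.** **Inputs**
- Expected effects 0.10 to 0.20 and OR 1.2 to 2.2; minima 0.13 and OR 1.36; 80% power; 432 persons per age group (3 × 144). All from the power section.
- Cluster ICC 0.10, individual ICC 0.2 to 0.4, retention 85/80/75% at waves 2 to 4. Same section.
- Alpha: not stated. Two-sided 5% is assumed, with one-sided 5% as a check.

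**1. Can the stated minima be reproduced?** Only roughly. An analytic generalised least squares variance for three communities and four waves, with the ICCs and retention above and no time effect in the model, gives a detectable effect of 0.114 to 0.144 (two-sided). This range contains 0.13. A logit-scale approximation gives an OR of about 1.37 to 1.38 at an outcome rate of 50%, close to 1.36. An exact match is not possible without the unstated inputs. Step 2 therefore takes the minima as given.

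**2. Power at the low ends, from the plan's own minima**

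At 80% power, minimum / SE = 1.960 + 0.842 = 2.802. Power at a smaller effect is Φ(2.802 × effect / minimum − 1.960), with odds ratios on the log scale.

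- Effect 0.10: 2.802 × 0.10 / 0.13 = 2.155; Φ(2.155 − 1.960) = Φ(0.195) = **0.58**.
- OR 1.2: ln 1.2 / ln 1.36 = 0.1823 / 0.3075 = 0.593; 2.802 × 0.593 = 1.661; Φ(1.661 − 1.960) = Φ(−0.299) = **0.38**.

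One-sided at 5%, the values are 0.61 and 0.43. At the upper ends (0.20 and OR 2.2) power is about 99% or more.

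**3. Sample size needed at the low ends**, other inputs unchanged, scaling as (minimum / effect)²:

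- 0.10: (0.13 / 0.10)² = 1.69; 432 × 1.69 ≈ 730 per age group.
- OR 1.2: (0.3075 / 0.1823)² ≈ 2.84; about 1,229 per age group.

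**4. Where do condom use and HIV testing lie?** Crude odds ratios from the Background rates:

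| Outcome | Group | Rates | Odds ratio |
|---|---|---|---|
| Condom use | Adults | 25% vs 12% | (0.25/0.75)/(0.12/0.88) = 2.44 |
| Condom use | Youth | 70% vs 49% | (0.70/0.30)/(0.49/0.51) = 2.43 |
| HIV test | Adults | 18% vs 10% | (0.18/0.82)/(0.10/0.90) = 1.98 |
| HIV test | Youth | 14% vs 7% | (0.14/0.86)/(0.07/0.93) = 2.16 |

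All four exceed 1.36. The low end of the binary range must therefore belong to other outcomes, which the article does not identify.

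**The case against.** The strongest defence is that the abstract ties sufficient power to condom use and HIV testing, and both clear the stated minimum comfortably. This stands, and it limits the weight of the point. It does not rescue the sentence, which covers all expected effects. Nor can the shortfall be assumed to touch only secondary outcomes. Table 1 puts two scales under a heading marked primary, and the continuous range may apply to them, although the article nowhere assigns 0.10 to either.

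A second defence is that an effect below the minimum can still be found. That is true, but 80% is the plan's own standard, and 58% and 38% do not meet it.

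A third is that the age groups are also analysed together. Simple scaling to 864 persons gives Φ(√2 × 2.155 − 1.960) ≈ 0.86 at 0.10, but only Φ(√2 × 1.661 − 1.960) ≈ 0.65 at OR 1.2. The sentence in any case speaks of the groups separately.

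A reader might go further and infer that HIV testing itself is underpowered, because control rates of 7% and 10% make OR 1.36 hard to detect. A small simulation (150 trials per setting, GEE instead of the planned mixed model, no wave effects) did give only 28% and 33% power for OR 1.36 at those rates. But 1.36 is the claimed minimum, not the expected HIV-testing effect. Backing the standard errors out of those results gives detectable odds ratios of about 1.87 and 1.76. The Background effects of 2.16 and 1.98 exceed these, with about 93% and 92% power. What remains is narrower: a single minimum of 1.36 does not hold at every outcome rate.

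**Conclusion.** The point holds as an internal contradiction. At the plan's own standard of 80%, the sample is not adequate for continuous effects from 0.10 up to 0.13 or for odds ratios from 1.2 up to 1.36, in adults and youth separately. Power at the two low ends is about 58% and 38%. The contradiction needs no assumption. The two percentages assume a two-sided 5% test and take the stated minima as correct.

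The article does not support extending this to condom use or HIV testing. On the stated minimum, their implied effects are detectable. Those odds ratios are crude, and the two for condom use lie above the plan's upper limit of 2.2, so the plan may have derived its expected values differently.

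Power also falls if time effects enter the model: the same analytic check then gives minima of 0.19 to 0.25. That is a separate question. The article does not say how its simulation handled time, and this verdict does not rest on it.

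**What to change.** Replace the concluding sentence of the power section with:

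*With 432 persons per age group the design has 80% power for effects of at least 0.13 (continuous) or OR 1.36 (binary, at the outcome rate assumed in the simulation: [state]). Expected effects below these values are not powered at 80% in adults and youth separately and will be reported as estimates with confidence intervals.*

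Then name the outcomes whose expected effects fall below these values, and say whether they include the self-efficacy scale or the communication index. If one of the ranges or minima is a misprint, correct that figure instead and keep the conclusion only if it then follows.

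A table of detectable odds ratios by outcome and age group would be useful, but it may be left to the full protocol or the SAP. The change needs no new data and no design change. Its cost is that the stated power becomes less favourable.

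### The power section claims power for all expected effects, but its own expected ranges start below its own minimum detectable values (0.10 against 0.13; OR 1.2 against OR 1.36)

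*Protocol article*

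**What the plan says.** All the relevant statements are in one paragraph of the protocol article, Methods, under the heading Power analysis, Aim 2 effectiveness.

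- **Expected effects:** "Expected effect sizes (0.10 to 0.20 for continuous outcomes; odds ratios ranging from 1.2 to 2.2 for dichotomous outcomes". The paragraph bases these on the team's efficacy study or, for HIV knowledge and STI prevalence, on a 2010 national survey.
- **Detectable effects:** for 432 persons in one age group, with 75% retained at the last wave and 80% power, the simulations "supported a minimum detectable effect size of 0.13 for continuous outcome variables, and a minimum detectable odds ratio of size 1.36".
- **Conclusion:** "Thus, we have sufficient power to detect all expected intervention effects for outcome variables for adults and youth separately".

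The simulation inputs are a cluster-level ICC of 0.10, an individual-level ICC of 0.2 to 0.4, and retention of 85%, 80% and 75% at waves 2 to 4. The paragraph does not print the significance level, the baseline event rates, or whether the simulated model contained a time effect.

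**The concern.** A minimum detectable effect at 80% power is the smallest true effect for which power reaches 80%; any smaller effect has less. The conclusion would therefore hold only if the smallest expected effect were at least as large as the minimum detectable one. For both outcome types it is smaller.

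This sentence is the article's verdict on whether the sample is large enough. The Aim 3 hypothesis expects significant improvement at each wave over a range of behavioural outcomes and STIs. Aim 4 then relates the effectiveness results to the judgement on the 3-Step Model. If an outcome at the low end of the expected range comes out non-significant, a reader told that the trial was powered for every expected effect has reason to take that as evidence of no effect. In fact such a result would be common even if the expected effect were real.

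The article does not say which outcomes sit at the low end. Table 1 puts the primary-outcome label on safer sex practices, a group that includes a self-efficacy scale and a partner communication index. Their expected effects are not printed, so it cannot be ruled out that a component under the primary label is affected.

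**Working it through.** **1. Direct comparison (no assumptions)**

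| Outcome type | Smallest expected | Minimum detectable, 80% power | Largest expected |
|---|---|---|---|
| Continuous | 0.10 | 0.13 | 0.20 |
| Binary (OR) | 1.2 | 1.36 | 2.2 |

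0.10 < 0.13 and 1.2 < 1.36. The gaps are too wide to be rounding.

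**2. Can the article's limits be reproduced?**

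Not uniquely, because alpha, event rates and the handling of time are not printed. An analytic generalised-least-squares variance was computed for a closed-cohort stepped wedge: 3 sites of 144, 4 waves, retention of 100/85/80/75%, cluster ICC 0.10 and individual ICC 0.2 to 0.4. The cluster was taken as community or as peer group. The limit is (z₀.₉₇₅ + z₀.₈₀) × SE, two-sided 5%. The binary case divides the SE by √(p(1−p)), an approximation, for rates p of 10% to 50%.

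| Model | Limit, continuous | Limit, OR | Power at 0.10 | Power at OR 1.2 |
|---|---|---|---|---|
| No period effects | 0.115 to 0.144 | 1.26 to 1.57 | 50% to 69% | 20% to 60% |
| Categorical period effects | 0.195 to 0.250 | 1.49 to 2.18 | 20% to 30% | 10% to 25% |

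The printed 0.13 and 1.36 are attainable without period effects. No variant brings power at 0.10 or OR 1.2 up to 80%. The smallest continuous limit found, even one-sided, is 0.102.

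**3. Power at the low end, taking the article's limits as exact**

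If 80% power is reached at a limit M, the implied SE is M / (z_α + z₀.₈₀), so the power at an effect E is

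Power = Φ[(z_α + z₀.₈₀) × E/M − z_α], with log odds ratios for binary outcomes.

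Two-sided 5% (assumed): z_α = 1.960, z₀.₈₀ = 0.842, sum 2.802.

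- Effect 0.10: Φ(2.802 × 0.10/0.13 − 1.960) = Φ(0.195) = 0.577
- OR 1.2: Φ(2.802 × ln 1.2/ln 1.36 − 1.960) = Φ(2.802 × 0.593 − 1.960) = Φ(−0.299) = 0.383
- OR 1.3: Φ(2.802 × ln 1.3/ln 1.36 − 1.960) = 0.667
- Top of the ranges: 0.991 at 0.20 and above 0.999 at OR 2.2

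One-sided 5%: 0.606 at 0.10 and 0.432 at OR 1.2.

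**4. Sample size that the claim would need**

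By inverse-square scaling, per age group:

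- 0.10: (0.13/0.10)² = 1.69; 1.69 × 432 ≈ 730
- OR 1.2: (ln 1.36/ln 1.2)² = 2.844; 2.844 × 432 ≈ 1,229

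This is only a gauge of the gap, not a proposal.

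**5. Scope: the named primary outcomes**

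Odds ratios from the efficacy-study rates in the Background:

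- Condom use, adults, 25% v 12%: (0.25 × 0.88)/(0.75 × 0.12) = 2.44
- Condom use, youth, 70% v 49%: (0.70 × 0.51)/(0.30 × 0.49) = 2.43
- HIV test, adults, 18% v 10%: (0.18 × 0.90)/(0.82 × 0.10) = 1.98
- HIV test, youth, 14% v 7%: (0.14 × 0.93)/(0.86 × 0.07) = 2.16

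All are above 1.36.

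**The case against.** The strongest reply is that this is one over-broad word. The Abstract makes a narrower claim, of sufficient power for condom use and HIV testing, and the Background rates put those outcomes well above OR 1.36. No sample size, outcome or model changes. This stands as a limit on scope: the error does not show that those two outcomes are underpowered. It does not make the sentence true. Nor are the Background rates clearly the planning values, since the condom-use odds ratios (2.43 and 2.44) exceed the top of the stated range (2.2).

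Other replies:

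- **The cluster ICC of 0.10 was conservative.** With the cited 0.05, the analytic continuous limit is 0.12 to 0.14 without period effects and 0.21 to 0.25 with them. It does not reach 0.10.
- **Adults and youth are also analysed together.** The sentence speaks of the groups separately. If doubling the sample shrank the SE by the full √2, the limits would be 0.13/√2 ≈ 0.09 and exp(ln 1.36/√2) ≈ 1.24. That would cover 0.10 but still not OR 1.2.
- **Youth recruitment was increased.** No number is given, the stated reason is that youth move away, and the adult sample is unchanged.
- **The power figures depend on an unprinted alpha and a normal approximation.** True, and they must be labelled so. The contradiction itself needs neither.
- **A printed range or limit may be the misprint.** Possible, and the fix allows for it. Until one is corrected, the three statements cannot all be right.
- **The plan has no rule that equates non-significance with no effect.** Also true. The misreading is a risk that the sentence invites, not something the plan prescribes.

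**Conclusion.** The concern holds. On the article's own figures, 80% power is available for effects of at least 0.13 and odds ratios of at least 1.36, not for all expected effects; that conclusion rests on nothing but the printed numbers. The size of the shortfall does rest on assumptions: with the printed limits taken as exact, a normal approximation and a two-sided 5% test, power at the bottom of the expected ranges is about 58% (0.10) and 38% (OR 1.2). With a one-sided 5% test it is about 61% and 43%. Which outcomes are affected cannot be determined from the article.

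One separate observation: 0.13 could be approached only with period effects left out of the calculation. The handling of time in the simulations should be stated when the figures are revisited, because including it would raise the limits further.

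**What to change.** 1. Check the expected ranges and the minimum detectable values against the simulation output. If one of them is misprinted, correct it.
2. If the figures stand, replace the concluding sentence. Say that, for adults and youth separately, 80% power is available for expected effects of at least 0.13 and odds ratios of at least 1.36. Add that power is lower below those limits: about 58% at 0.10 and 38% at OR 1.2 if the test is two-sided at 5%.
3. State the significance level and sidedness used in the simulations.
4. List the outcomes, by age group, whose expected effect lies below the limits, including any component under the primary label. Say that these will be reported by estimate and confidence interval, and that a non-significant result will not be read as absence of effect.

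The cost is one rewritten sentence and a short list. No participants, data or analyses are added. The stated power becomes less favourable for the weaker expected outcomes.
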